### Patient and public involvement

Patients and/or the public were not involved in the design, conduct, reporting or dissemination plans of this research.

### Eligibility criteria

We attempt to enrol all eligible children in each compound that either previously participated in the MapSan trial, has previously received an intervention latrine, or meets the original enrolment criteria for MapSan control compounds.^34^ Participant inclusion criteria include:

Child aged 29 days to 60 months old.Born into and residing in a compound enrolled in the 5-year follow-up study; in intervention compounds, the child must have been born following the delivery of the sanitation intervention.Has continuously resided in the study compound for the preceding 6 months, or since birth if under 6 months of age.Has a parent or guardian who is able to understand and complete the written informed consent process and allow their child to participate.

Children are excluded if they have any caregiver-indicated medical condition or disability that precludes participation in the study.

### Participant enrolment

Enrolment is conducted by trained study staff in either Portuguese or Changana, according to the respondent’s preference, with written materials provided in Portuguese. We first obtain verbal consent from the compound leader to approach households in the compound for enrolment. We then seek written, informed consent to participate from the parent or guardian of each eligible child. Participation is entirely voluntary; guardians may decline their child’s participation for any reason and can withdraw their child at any point. We began enrolling participants on 28 March 2022.

### Household visits and procedures

After locating study compounds, the household of a participating child is visited twice, typically on consecutive days. On the first day, trained study staff conduct written consent procedures; administer compound, household, and child questionnaires; record child anthropometry measures; collect environmental samples; and request the child’s caregiver to retain a sample of the child’s stool. The household is revisited the following day to collect a stool sample from the child and complete environmental sample collection. If the stool sample is unavailable, the study staff coordinate an additional visit to retrieve the stool. In the event that 7 days pass since the initial visit without collection of a stool sample, a qualified nurse visits the child to obtain a rectal swab.

After collection of the stool sample, deworming is offered to all household members >1 year old who have not been dewormed in the past year, unless pregnant or breast feeding. Deworming consultation and medication provision is conducted by Ministry of Health staff following the national guidelines for deworming procedures. Deworming is offered in-kind to all household members and leverages the household interaction to provide an important public health service. Besides deworming, this study offers no direct benefit to children participating in this study. No incentives are provided to study participants, but we provide 50 meticais (approximately US$1) of mobile phone credit on the caregiver’s preferred network for each child to compensate for the costs incurred in communicating with the study team to arrange household visits. Households from which we collect food and/or large-volume water samples are reimbursed 50 additional meticais to offset these expenses.

### Environmental sample collection

We are sampling environmental compartments at a randomly selected subset of 100 intervention and 100 control compounds to represent compound-level and household-level exposures.^37^ At the entrance to the compound latrine we collect soil, flies, and a large volume air sample, as well as faecal sludge from the latrine or septic tank and any animal faeces observed in the shared outdoor space.^49 50 56 57^ One household is randomly selected among those households with children enrolled in the child health study, from which we collect swabs of flooring at the household entrance, flies in cooking area, prepared child’s food, stored drinking water, and water from the household’s primary source.^52 58 59^

We are also collecting environmental samples from the public domain to conduct environmental surveillance of pathogens circulating in the community^56 60^; such samples are not linked to specific individuals in any way. Sample matrices are informed by the compartments on Maputo’s Excreta Flow Diagram,^61^ including wastewater, surface and open drain water, soils in the vicinity of solid and faecal waste disposal locations, and wastewater effluent from hospitals treating COVID-19 patients. We identify sample locations using satellite imagery in consultation with technicians responsible for sanitation and drainage in Maputo. Samples are collected with written permission from the municipal government on a weekly basis for matrices with a single available sampling location (eg, wastewater treatment plant influent) and twice at all other locations (once in each the rainy and dry seasons) to prioritise the geographic distribution of sampling locations across Maputo city. We aim to collect approximately 100 samples of solids (soil, faecal sludge), 100 large-volume liquid samples (wastewater, surface water, and open drains),^62^ and 100 passive samples of liquids.^60^

### Study outcomes

#### Enteric pathogen detection in stool

Stool-based molecular detection is performed for 27 enteric pathogens commonly implicated in both symptomatic and asymptomatic childhood infections globally, including those identified at the Global Enteric Multicenter Study site in Manhiça, Mozambique.^12 36 56 63^ Reverse-transcription quantitative PCR is conducted by custom TaqMan Array Card (TAC; Thermo Fisher, Carlsbad, California, USA) to simultaneously quantify genetic targets corresponding to 13 bacterial pathogens (*Aeromonas* spp, *Campylobacter jejuni*/*coli, Clostridioides difficile, E. coli* O157, enteroaggregative *E. coli* (EAEC), enteropathogenic *E. coli* (EPEC), enterotoxigenic *E. coli* (ETEC), Shiga toxin-producing *E. coli* (STEC), enteroinvasive *E. coli* (EIEC)/*Shigella* spp, *Helicobacter pylori, Plesiomonas shigelloides, Salmonella enterica, Vibrio cholerae*), 4 protozoan parasites (*Cryptosporidium* spp, *Cyclospora cayetanensis, Entamoeba histolytica, Giardia* spp), 5 STH (*Ascaris lumbricoides, Ancylostoma duodenale, Necator americanus, Strongyloides stercolaris, Trichuris trichiura*) and 5 enteric viruses (adenovirus 40/41, astrovirus, norovirus GI/GII, rotavirus, sapovirus).^64^ We also include the respiratory virus SARS-CoV-2 on the custom TAC to support surveillance through faecal waste streams.^65 66^

Our primary outcome is the prevalence of a prespecified subset of 22 enteric pathogens, including *Shigella* spp and *T. trichiura*, the two pathogens most impacted at 24 months among children born after the intervention was delivered.^34^ As in the original MapSan study, we exclude enteric viruses from the primary outcome due to greater potential for direct contact transmission, which is unlikely to be impacted by the intervention.^34 47 67^ Because we anticipate a combined prevalence (detection of at least one pathogen in a given stool sample) near 100%, and the intervention could plausibly increase the prevalence of some pathogens while reducing others, we do not define a composite prevalence outcome.^34 68^ Rather, we will estimate the effect of the intervention on the prevalence of each pathogen individually, along with a pooled estimate of the intervention effect across the outcome set to serve as a summary of intervention’s impact on pathogen prevalence that is directly comparable to the individual effect estimates.^69 70^ The pooled effect of a single intervention across a set of related outcomes may be thought of as the treatment effect on a generic enteric pathogen. The pathogens for which individual effects can be more precisely estimated (such as those with higher background prevalence) contribute more to the pooled estimate, which is recovered alongside the individual effects for each pathogen and shares the same scale, allowing this summary metric to be directly interpreted in the context of its components, augmenting rather than replacing the individual estimates. This stands in contrast to composite outcomes, which construct new metrics that are related to, but fundamentally differ from, their component outcomes—the prevalence of *any* pathogen being conceptually distinct from the prevalence of a particular pathogen, for instance.

Secondary outcomes include the individual prevalence and the continuous gene copy density in stool of all 27 enteric pathogens assessed on TAC, including enteric viruses. Recognising the potential challenges to interpretation due to pervasive exposure, persistent infection and rapid reinfection, and possible protective effects,^71–74^ we will also repeat the primary outcome analysis excluding *Giardia* from the outcome set.

#### Anthropometry

Child weight and recumbent length (child age <24 months) or standing height (24–60 months) are assessed according to standard WHO protocols and transformed to age-adjusted z-scores using WHO reference populations to obtain height-for-age (HAZ), weight-for-age (WAZ), and weight-for-height (WHZ) z-scores.^75 76^ Secondary outcomes include continuous HAZ, WAZ, and WHZ, as well as prevalence of binary growth outcomes stunting (HAZ <−2), underweight (WAZ <−2), and wasting (WHZ <−2).^13^

#### Caregiver reported illness

Caregiver surveys are administered to ascertain child diarrhoeal disease, defined as the passage of three or more loose or watery stools in a 24-hour period, or any bloody stool, in the past 7 days.^77^ We also assess two caregiver-reported negative control outcomes for each child: the 7-day period-prevalence of bruises, scrapes, or abrasions and the 7-day period-prevalence of toothache.^78^ We do not expect the intervention to impact either child bruising or toothache prevalence, so significant differences in these outcomes by treatment arm would suggest possible bias in our caregiver-reported outcomes.

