## Introduction

There is a high burden of childhood enteric infections associated with poor environmental conditions, with multiple enteric pathogens frequently detected in stool within the first year of life.^1–3^ This is also the period with the highest incidence of diarrhoea, which remains a leading cause of child mortality in low-income and middle-income countries and has long been associated with stunted growth.^4–6^ However, many diarrhoeal episodes are not attributable to infectious aetiologies,^3 7^ while the aetiology of attributable diarrhoea varies widely by setting and only certain diarrhoeal pathogens are consistently implicated in reduced linear growth.^2 8 9^ Far more prevalent is asymptomatic enteric pathogen shedding in stool,^3 7 10–14^ which may be more strongly associated with poor growth than diarrhoeal illness,^2 15–17^ potentially by contributing to intestinal inflammation, gut permeability, and nutrient malabsorption in a condition known as environmental enteric dysfunction (EED).^18–21^ In addition to the diverse negative impacts of stunting,^22^ specific adverse health outcomes associated with enteric infection and EED include delayed cognitive development^23–25^ and reduced oral vaccine efficacy.^26 27^

Water, sanitation and hygiene (WASH) interventions aim to prevent diarrhoea and improve child growth by interrupting faecal-oral pathogen transmission.^28^ However, recent rigorous WASH intervention trials have demonstrated inconsistent and often limited impacts on child health.^13 29–34^ Methodological limitations of the distal outcome measures used notwithstanding,^35 36^ these findings are consistent with the interventions insufficiently interrupting environmental transmission and exposure to enteric pathogens.^37^ Combined WASH interventions with high fidelity and adherence reduced stool-based detection of *Giardia*, hookworm and possibly *Ascaris* among 30-month-old children (but not younger children) and enteric viruses in rural Bangladesh,^10 38 39^

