#### Growth and caregiver-reported outcomes

The effects of the intervention on mean HAZ, WAZ, and WHZ; the prevalence of stunting, underweight, and wasting; and the period-prevalence of caregiver-reported diarrhoea and negative control outcomes (bruising, scrapes, and abrasions; toothache) will be analysed separately as secondary outcomes using generalised estimating equations and robust standard errors with exchangeable correlation structure and clustering by compound (the level at which the sanitation intervention was delivered).^13 34 101^ The estimated difference in age-adjusted z-scores by treatment assignment will be used as the measure of effect for continuous anthropometry outcomes. The PR will be estimated by modified Poisson regression for binary growth status and caregiver-reported outcomes. We will not adjust for multiple comparisons.^31 102^

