#### Covariates and effect measure modification

As a cross-sectional study of an existing intervention, all analyses will be adjusted for a set of covariates selected a priori as potential confounders of the sanitation-enteric pathogen shedding relationship.^103^ The adjustment set will include child age and sex, caregiver’s education, and household wealth index; additional covariates will be considered in exploratory adjusted analyses.^10 11 34 104^ Records missing covariate data will be excluded from primary analyses. Analyses will be repeated with missing data imputed by multivariate imputation using chained equations (MICE) as a sensitivity analysis.^34 105^ In addition to covariates, caregiver-reported outcomes and continuous growth outcomes (HAZ, WAZ, and WHZ) will be used for imputation; derived binary growth statuses (stunting, underweight, and wasting) will be recalculated for each observation after conducting imputation procedures. Missing pathogen outcomes will not be imputed, nor will pathogens be used to inform imputation of other variables. However, datasets containing imputed covariates will be joined to observed pathogen outcomes by unique child identifier for sensitivity analyses; the Bayesian hierarchical models will be fit to each imputed dataset and draws from the posterior predictive distributions for parameters and contrasts of interest will be concatenated to obtain pooled estimates across the multiple imputed datasets.^106^ The specific enteric pathogens detected are expected to be strongly related to child age.^8 34^ We will examine effect measure modification of the primary and secondary outcomes stratifying by age group (1–11 months, 12–23 months, and 24–60 months).^3 107^

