Because childhood diarrhoea is a leading cause of child mortality, selection bias arising from survivor effects may be present in our sample, particularly among older age groups.^109^ However, loss to follow-up due to mortality was exceptionally rare in the previous assessment—far less common than emigration, which was not previously differential by treatment arm.^34^ Our use of stool-based enteric pathogen detection as an objective primary outcome mitigates the potential for measurement bias^36^ and we are assessing multiple negative control outcomes to account for potential response bias in our secondary caregiver-reported outcomes.^78^ As a long-term evaluation of an existing intervention, the potential for exposure measurement error is low—interventions that have degraded substantially may shift results towards the null, but in so doing would represent a valid assessment of intervention sustainability.^110^ The potential for exposure misclassification among controls is higher, in that they may have independently upgraded to sanitation infrastructure comparable to the intervention. We are actively monitoring this possibility at all study sites; have prespecified criteria for identifying sites achieving such conditions; and will conduct sensitivity analyses with these sites excluded, considered as controls, and considered as equivalent to the intervention to characterise the impact of any such potential exposure misclassification among controls.

A key challenge is identifying an appropriate set of outcomes against which to evaluate the intervention; in this regard, we preferred inclusivity given the pathogens likely to be observed in our study setting, at the risk of unduly shifting our eventual results towards the null. This challenge persists, regardless of study design, so long as the study aims include assessing the effect of some condition or intervention on exposure to, or infection by, multiple pathogens that share a common route of transmission.^111^

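### Toothache is used as a negative control from 29 days of age, and both negative controls are read only by significance, so a null result is weak reassurance if they are clearly rarer than diarrhoea

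*Protocol article*

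**What the plan says.** The section on caregiver reported illness states: "We also assess two caregiver-reported negative control outcomes for each child: the 7-day period-prevalence of bruises, scrapes, or abrasions and the 7-day period-prevalence of toothache". It expects no intervention effect on either, and adds that "significant differences in these outcomes by treatment arm would suggest possible bias in our caregiver-reported outcomes". No other rule for reading them appears in the article.

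The eligibility criteria set the age range: "Child aged 29 days to 60 months old". No narrower range is given for either control. Under growth and caregiver-reported outcomes, "caregiver-reported diarrhoea and negative control outcomes (bruising, scrapes, and abrasions; toothache) will be analysed separately as secondary outcomes", by generalised estimating equations clustered on compound; "The PR will be estimated by modified Poisson regression for binary growth status and caregiver-reported outcomes", without multiplicity adjustment. The section on covariates and effect measure modification stratifies primary and secondary outcomes by age: 1–11, 12–23 and 24–60 months.

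The Limitations section relies on these items: "we are assessing multiple negative control outcomes to account for potential response bias in our secondary caregiver-reported outcomes". The study design section says that neither staff nor participants can be blinded. Of the first year of life, the Introduction says: "This is also the period with the highest incidence of diarrhoea".

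**The concern.** A negative control informs about bias in another outcome only if it can occur, and be reported, in the children concerned. Toothache needs teeth and a child who can make the pain known, so in young infants it is close to a structural zero. The bruising item depends largely on mobility: probably uncommon in the first months, possible later in the first year. Direct support from the controls is therefore thinnest in the age group where the Introduction expects most diarrhoea, and that group is analysed as a stratum.

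The second issue is the reading. Significance depends on how common the control is as well as on how large the bias is. For a rare control, a non-significant result is expected with or without moderate bias. The study is unblinded and these items are its named safeguard against response bias, so an uninformative null could be taken as support for the diarrhoea result.

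**Working it through.** **1. The plan's own figures.** The section on minimum detectable effect size covers pathogen prevalence only. They reproduce closely with a variance per arm of [p(1−p)/m + 0.05]/K (K compounds, m children per compound), 80% power and two-sided 5%:

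- 25% reduction: baseline prevalence of about 33% (K = 300, m = 2.5) and 46% (K = 200, m = 2), against 34% and 46% stated.
- 95% reduction: about 6% to 8%, against the stated minimum of 6–8%.

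On that convention, a control rarer than 6–8% could not reach 80% power for any reduction. But an added variance of 0.05 exceeds p(1−p) = 0.0475 at p = 0.05, so the convention is very conservative for rare outcomes. The steps below use a design effect instead.

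**2. Power of one control against a modest bias.** From the documents: 400 per arm (200 compounds × 2 children). Assumed: ICC 0.05 (the article gives values below 0.1, for pathogens only), bias PR 0.8, control prevalence 3–10%. Design effect = 1 + (2−1) × 0.05 = 1.05.

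Var(log PR) = 1.05 × [(1−p0)/(400·p0) + (1−p1)/(400·p1)], with p1 = 0.8·p0.

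At p0 = 0.03: 1.05 × (0.97/12 + 0.976/9.6) = 0.192, SE 0.438. |ln 0.8| = 0.223, and 0.223/0.438 = 0.51. Power = Φ(0.51−1.96) + Φ(−0.51−1.96) = 8%.

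95% CI when the observed PR is 1, at 3%: SE = √(1.05 × 2 × 0.97/12) = 0.412, and exp(±1.96 × 0.412) = 0.45 to 2.24.

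| Control prevalence (assumed) | Power for PR 0.8, 400 per arm | 95% CI around PR 1, 400 per arm | Power for PR 0.8, 750 per arm (design effect 1.075) |
|---|---|---|---|
| 3% | 8% | 0.45–2.24 | 11% |
| 5% | 10% | 0.54–1.86 | 15% |
| 10% | 16% | 0.65–1.53 | 26% |
| 20% | 30% | 0.75–1.33 | 49% |

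**3. Would the controls flag a bias large enough to make diarrhoea significant?** Assume the same bias PR acts on every reported item, the two controls are independent, and there are 400 per arm (400/1.05 = 381 effective). A two-proportion test gives:

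- Diarrhoea at 10%: bias must reach PR 0.47 for an 80% chance of a significant diarrhoea result. Toothache at 1%, 3% or 5% flags that bias with probability 13%, 32% or 49%. Bruising at 5%, 10% or 20% flags it with probability 49%, 80% or 99%. At least one control flags it with probability 56% (toothache 1%, bruising 5%) up to 99% (bruising 20%).
- Diarrhoea at 15%: bias must reach PR 0.565. At least one control flags it with probability 41% (1% and 5%) up to 92% or more (bruising 20%).

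The result turns on whether the controls are rarer than diarrhoea.

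**4. The infants.** If ages were uniform over 1–60 months, the 1–11 month stratum would hold 11/59 = 19% of children, or 71 (381 × 11/59) to 130 (698 × 11/59) effective children per arm, where 698 = 750/1.075. Power there for a bias of PR 0.6 is 5–7% at 1–2% prevalence and 14–22% at 10%. In the whole sample infants matter little: if that 19% are all zeros, dropping them leaves power for PR 0.6 at about 25% when prevalence is 5% in the older children, and raises it from 78.0% to 79.5% when it is 20%.

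**The case against.** A reader might infer that the two controls cannot serve at all, or are unlikely to reveal a bias large enough to create a diarrhoea effect. The documents do not support either reading. They give no prevalence for toothache, bruising or diarrhoea. The bruising item is broad, covers visible injury, needs no speech from the child and is asked up to 60 months. At 20% prevalence and 400 per arm it would flag PR 0.6 with 84% power by the formula in step 2. The low powers at PR 0.8 also do not settle the matter: at 10% prevalence a bias of that size would make diarrhoea itself significant only 16% of the time.

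Nor do infants explain weakness in the overall test; step 4 shows that removing them changes almost nothing. The reporter is the caregiver, so controls in older children still say something about reporting by arm. The article never says that a non-significant control clears diarrhoea of bias, and it will estimate PRs, so magnitude will be available. The data analysis plan, not shown here, may say more.

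All of this stands and narrows the point. What remains rests on what the article itself fixes: toothache assessed in every child from 29 days, a 1–11 month stratum for secondary outcomes, and significance as the one stated reading.

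**Conclusion.** The concern holds in a limited, conditional form. The toothache check in the 1–11 month stratum is close to empty, and bruising gives only partial cover there. Across all ages, if both controls are clearly rarer than diarrhoea, a non-significant result says little: power is 8–16% for PR 0.8 at 400 per arm with 3–10% prevalence, and 11–26% at 750 per arm. If bruising is about as common as diarrhoea or more so, and bias acts equally on all reports, the check is adequate for a bias that would make diarrhoea significant.

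The sizes rest on assumed prevalences and an assumed ICC of 0.05. The consequence is confined to the secondary caregiver-reported diarrhoea outcome; the stool-based primary outcome is unaffected.

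**What to change.** 1. Analyse toothache only in children old enough to have and report it (for example 12 months and over), and do not fit it in the 1–11 month stratum. This makes the comparison meaningful; it does not add power.
2. Replace the significance reading. Report the PR and 95% CI for each control beside the diarrhoea PR estimated in the same children.
3. State that reporting bias of that size is not excluded when the control CIs contain the diarrhoea PR.
4. State that the diarrhoea result under 12 months has little direct negative-control support.

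This changes analysis and reporting wording only; the planned models already give the PRs. The downside is a more cautious statement about one secondary outcome.
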